### Sample size

The calculated sample size was based on detecting the main factorial effects of each factor on Multidimensional Fatigue Inventory (MFI) Physical Fatigue (PF) after completed intervention [32–34]. The target main effect size was determined to be 2, which according to Purcell et al. [35] is the minimal clinically important difference for the MFI-PF. We assumed that the standard deviation (SD) of PF was 5 in all four treatment arms, which is the SD reported in Purcell et al. [35], Hagelin et al. [36] and in an ongoing study within our research group (manuscript in preparation). Because three tests (two main and one interaction effect) were planned, the 5% significance level was adjusted using Bonferroni correction. In order to have 80% power to detect a main factorial effect of 2 under the null hypothesis of no effect, 67 individuals in each of the four treatment arms are needed, with a total sample size of 268 individuals.

Further adjustments of the sample size were necessary for several reasons. First, the sample size calculation was based on the assumption of no interaction effects. However, Montgomery et al. [29] argue that, if anticipating quantitative interactions, the trial should be powered to detect those effects. Interaction effects often are much smaller in size compared to the main effects. In clinical trials, it is therefore rare to have 80% power to detect the interaction effect. For instance, given the calculated sample size in the present study, the trial would have a power of only 22% to detect an interaction effect of 1. However, in the present study a possible interaction between the factors is of clinical interest. Thus, the original sample size was doubled, increasing the power to detect the interaction between to approximately 50%. Second, to account for missing data and drop-outs, the original sample size was increased further by 30%. Third, given that we include a baseline assessment, and assuming a moderate correlation (0.3) between the MFI-PF at baseline and follow-up assessments, the sample size can be reduced by approximately 10% [37]. Combining the above, we concluded that including approximately 150 individuals in each treatment arm, 600 individuals in total, should meet the statistical requirements of the trial.

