### Statistical analysis

The data will be analysed according to the intention-to-treat (ITT) principle, i.e. all participants will be analyzed as randomized, regardless of whether they complete the intervention as planned. The primary parameters of interests are the three factorial effects (2 main and one interaction) after completed intervention. Each factorial effect will be estimated taking into account the stratified design following Imbens and Rubin [53]. Thus, we will provide estimates for the overall factorial effects, which are the primary parameters of interest, and also stratum-specific factorial effects which could facilitate external validity. Baseline measurements will be included in the analysis model to increase the precision of the estimates.

Drop-outs and missing values will be handled according to the following procedure. The main analysis will be based on data where missingness is handled using multiple imputations by chained equations. The specification of the multiple imputation model (e.g. choice of auxiliary variables) will be decided after comparing the subject characteristics in those with complete and incomplete data. Under the assumption of missing at random (MAR), an analysis based on multiple imputation conforms with the ITT. Due to the assumption of MAR, which could be a strong assumption to make, factorial effects will also be estimated using complete blocks only. This is a result from the permuted block design which allows for unbiased estimation of the factorial effects using the complete blocks only. Sensitivity analysis will conducted by comparing estimates from the two analyses above with estimates based on complete cases only, a pattern-mixture model, and tipping points analyses [54].

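### Holm's step-down would keep the same 5% family-wise error as the plan's Bonferroni adjustment and never reject less; the gain for the interaction depends on the main effects (optional, low severity)

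*Protocol article*

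**What the plan says.** The Sample size section of the protocol article gives the reason and the rule together: "Because three tests (two main and one interaction effect) were planned", "the 5% significance level was adjusted using Bonferroni correction". The planning inputs are "The target main effect size was determined to be 2" and "We assumed that the standard deviation (SD) of PF was 5 in all four treatment arms", with 80% power, and the result is "67 individuals in each of the four treatment arms are needed, with a total sample size of 268 individuals".

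The same section then turns to the interaction. At that size, "the trial would have a power of only 22% to detect an interaction effect of 1". Because the interaction is of clinical interest, the section continues: "Thus, the original sample size was doubled, increasing the power to detect the interaction between to approximately 50" per cent. A 30% allowance for missing data and drop-out, and a reduction of about 10% for a baseline correlation of 0.3, lead to about 600 participants.

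The Statistical analysis section gives all three effects the same standing: "The primary parameters of interests are the three factorial effects (2 main and one interaction) after completed intervention". It names no multiplicity procedure of its own.

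**The concern.** Plain Bonferroni tests each effect at 0.05/3 = 0.0167 whatever the other two show. Holm starts at the same 0.05/3 for the smallest p-value. If that is rejected it moves to 0.05/2 for the next, and if that is rejected to 0.05 for the last. It controls family-wise error at 5% under any dependence between the tests and cannot reject less than Bonferroni.

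The interaction is the test that the plan itself treats as weak, and the original sample was doubled from 268 to 536 on its account. If the main effects are real, Bonferroni gives up power on that test which a different rule would keep with no added participants and no added error.

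**Working it through.** **Inputs from the Sample size section.** Family-wise level 5% over three tests; main effect 2; interaction 1; SD 5; 67 per arm (268 in total); doubled to 536; 30% allowance; baseline correlation 0.3; 600 in total.

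**Assumptions.**
- Tests are two-sided. The article does not say so, but two-sided testing gives 131 per factor level, close to the stated 134, and one-sided testing gives 111.
- The four arms are equal, so the three contrasts are orthogonal and their test statistics are treated as independent.
- The analysis carries the information of 420 participants (600 × 0.7) in the main case, with 536 as the upper comparison.

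**1. Reproduce the plan's figures.** With N participants in equal arms, each contrast has SE = √(4 × 5²/N) = √(100/N). Power ≈ Φ(effect/SE − z), with z = 2.394 at two-sided 0.05/3.
- Main effect of 2, N = 268: SE = 0.611, power 81.1% (80.6% with the t distribution; 66 per arm gives 79.9%). This matches 67 per arm.
- Interaction of 1, N = 268: power 22.5%, matching the stated 22%. At 0.05 it would be 37.3%, so the plan applied 0.05/3 to the interaction as well. Taking 1 as the raw difference of differences would give about 6%, so the plan's interaction is half that difference and has the same SE as a main effect.
- Interaction of 1, N = 536: 46.9%, or 51.3% with baseline adjustment, on either side of the stated figure of about 50%. At 0.05 without adjustment it would be 63.9%.

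**2. Holm's power for the interaction.** Let P₁, P₂, P₃ be the interaction's power at 0.05/3, 0.025 and 0.05. Let A be the probability that at least one main effect has p ≤ 0.05/3. Let B be the probability that both main effects have p ≤ 0.025 and at least one has p ≤ 0.05/3. With independent contrasts,

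Holm power = P₁ + (P₂ − P₁) × A + (P₃ − P₂) × B.

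**3. Put the numbers in: 420 analysed, correlation 0.3.** SE = √(100 × (1 − 0.3²)/420) = √(91/420) = 0.4655. For an interaction of 1, P₁ = 0.403, P₂ = 0.463 and P₃ = 0.575.

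With both main effects equal to 2, A = 0.999 and B = 0.961, so power = 0.403 + 0.060 × 0.999 + 0.112 × 0.961 = 0.570. The other rows follow in the same way.

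| True main effects | A | B | Bonferroni | Holm |
|---|---|---|---|---|
| 2 and 2 | 0.999 | 0.961 | 40.3% | 57.0% |
| 2 and 0 | 0.972 | 0.024 | 40.3% | 46.4% |
| 1 and 1 | 0.644 | 0.211 | 40.3% | 46.5% |
| 1 and 0 | 0.413 | 0.011 | 40.3% | 42.9% |
| 0.5 and 0.5 | 0.179 | 0.014 | 40.3% | 41.5% |
| 0 and 0 | 0.033 | 0.001 | 40.3% | 40.5% |

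Simulation of three independent normal contrasts agrees to within about 0.2 points.

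**4. Other sizes.** With 536 analysed and correlation 0.3, Bonferroni gives 51.3%. Holm gives 67.9% with main effects 2 and 2, 57.6% with 2 and 0, and 51.5% with 0 and 0. Without baseline adjustment and with main effects 2 and 2, the change is from 36.5% to 52.9% at 420 and from 46.9% to 63.7% at 536.

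**5. Main effects and error rate.** At 420 with correlation 0.3, power for a main effect of 2 (the other also 2, interaction 1) rises from 97.1% to 98.5%. Holm's simulated family-wise error was at most 4.97% in every null configuration tried.

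**The case against.** The strongest reply has four parts.

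- **Bonferroni is not wrong.** It controls the error rate, it reproduces the plan's figures, and the article openly accepts limited power for the interaction. This stands in full.
- **The adjustment is stated in the sample-size paragraph.** A reader might infer that the article commits the final analysis to 0.0167 per test. That is plausible, since it is the only rule named and the interaction power uses it, but it is not established. A statistical analysis plan that is not shown could name another procedure.
- **The large gain is the favourable case.** A reader might infer from the near-certain power for the main effects at 600 that the interaction would usually be tested at 0.025 or 0.05, and so that the lost power is simply recovered. The article does not support this. The value 2 is presented as the minimal clinically important difference, not as an expected effect; all four arms exercise; and the Background calls the trial evidence inconsistent and the best intensity unclear. High power at an assumed effect does not mean that the effect exists. This stands: outside the case of two effects of 2, the gain in the table is about 0 to 6 points.
- **Holm has a reporting cost.** Each extra rejection has a p-value between 0.0167 and 0.05, so its 98.3% Bonferroni interval includes zero. With both main effects at 2 and 420 analysed, the interaction is in that position in about 17% of trials (57.0% − 40.3%), which is the whole of the gain. Wanting tests and intervals to agree is a legitimate reason to stay with Bonferroni.

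None of this removes the basic fact that Holm never rejects less at the same family-wise error.

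**Conclusion.** The point holds as an optional improvement of low severity. The only multiplicity rule in the article is plain Bonferroni, and Holm is at least as powerful at the same 5% family-wise error. At 420 analysed, SD 5, correlation 0.3 and an interaction of 1 on the plan's scale, interaction power goes from 40% to 57% if both main effects are 2, to 46% if one is, to about 47% if both are 1, and does not materially change if neither is real. Main-effect power changes by only one or two points.

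These figures rest on two-sided tests, equal arms and the plan's own SD and correlation. They do not show an error in the control of type I error or in the sample size: Holm's first step is also 0.05/3, so the calculation of 268 is unaffected.

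**What to change.** Optional. Keep the Bonferroni sample-size calculation as it is. In the Statistical analysis section, before unblinded results are seen, state that the three factorial hypotheses on MFI Physical Fatigue after completed intervention are tested by Holm's procedure at an overall two-sided 5%, and that Holm-adjusted p-values will be reported.

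State in advance that Holm has no simple matching simultaneous intervals, so an effect rejected only by Holm will have a 98.3% Bonferroni interval that includes zero. Report unadjusted 95% intervals alongside, labelled as unadjusted.

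The cost is a sentence or two of text, no participants, and this possible mismatch between test and interval. If the investigators value agreement between tests and intervals more than the conditional gain in power, keeping Bonferroni is defensible; the Statistical analysis section should then say so.

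### The 30% drop-out allowance does not protect the doubled sample: with 600 randomised, interaction power is about 40–44%, not the approximately 50% that justified the doubling

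*Protocol article*

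**What the plan says.** All the figures are in the protocol article, Methods, Sample size.

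- Effect and spread: "The target main effect size was determined to be 2" on MFI Physical Fatigue, and "We assumed that the standard deviation (SD) of PF was 5 in all four treatment arms".
- Error rate: "Because three tests (two main and one interaction effect) were planned, the 5% significance level was adjusted using Bonferroni correction".
- Base size for 80% power on a main effect: "67 individuals in each of the four treatment arms are needed, with a total sample size of 268 individuals". At that size the plan gives 22% power for an interaction of 1.
- Because the interaction is of clinical interest, "the original sample size was doubled, increasing the power to detect the interaction between to approximately 50" per cent.
- For missing data and drop-outs, "the original sample size was increased further by 30" per cent.
- For baseline adjustment, assuming a correlation of 0.3, "the sample size can be reduced by approximately 10" per cent.
- Conclusion: "including approximately 150 individuals in each treatment arm, 600 individuals in total, should meet the statistical requirements of the trial".

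The Statistical analysis section names the two main effects and the interaction as the primary parameters. Its main analysis uses multiple imputation by chained equations.

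**The concern.** The only reason given for doubling the trial is interaction power, and approximately 50% is the only interaction power given for anything larger than 268. A drop-out allowance exists to keep the power reached in the step before it. Here the allowance is described as a percentage of the original sample size, although by then the number to protect is the doubled one. Thirty per cent of 268 is far less than 30% of 536.

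If the loss rate is meant for the whole trial, 600 does not keep the power the doubling was meant to buy. The interaction is one of three primary parameters, so its expected power affects how a non-significant result should be read. At 40% power, a true interaction of 1 would be missed in about 60% of such trials.

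**Working it through.** **Inputs (all from Sample size).** Main effect 2; interaction effect 1; SD 5; alpha 0.05/3 = 0.0167 per test; baseline correlation 0.3, so a variance factor of 1 − 0.3² = 0.91. The section does not state sidedness; two-sided is assumed (critical value 2.394). Each factorial contrast compares N/2 with N/2, so SE = √(4 × 25/N) = √(100/N), or √(91/N) with baseline adjustment. Power ≈ Φ(effect/SE − 2.394).

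**Reproducing the plan's own figures.**
- Base size: 2 × (2.394 + 0.842)² × 25/2² = 131 per factor level, or 65.5 per arm. With the t distribution, power is 79.9% at 66 per arm and 80.6% at 67, so 67 per arm and 268 in total reproduce.
- Interaction of 1 at 268: SE = 0.611, power 22.5%. The stated 22% reproduces, which confirms the scale. Reading the 1 as a raw difference of differences would give only about 6%.
- Interaction of 1 at 536: SE = 0.432, power 46.9%. The plan's approximately 50% is this figure rounded up.

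**Reaching 600.**

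| Reading | Arithmetic | Total |
|---|---|---|
| Every percentage taken on 268 and added | 268 × (2 + 0.3 − 0.1) | 590 |
| 30% on 268, then 10% off the sum | (536 + 80) × 0.90 | 555 |
| Steps applied in turn to the doubled sample | 536 × 1.3 × 0.90 | 627 |
| Doubled sample protected against 30% loss | 536/0.70 × 0.90 (or × 0.91) | 689 (697) |

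The first reading gives 147 per arm, which fits approximately 150. Its allowance is 0.3 × 268 = 80 people, and 80/600 = 13%.

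**Power with 600 randomised, baseline adjustment credited in full.**

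| Analysed | How it arises | SE | Power, interaction of 1 | Power, main effect of 2 |
|---|---|---|---|---|
| 520 | 600 − 80 | 0.418 | 49.8% | 99% |
| 462 | 600/1.3 (23% lost) | 0.444 | 44.4% | 98% |
| 420 | 600 × 0.70 (30% lost) | 0.465 | 40.3% | 97% |

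Without baseline adjustment, the interaction figures at 462 and 420 fall to 40.3% and 36.5%.

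**How much loss 600 can bear.**
- To keep the 47% of the doubled sample: 536 × 0.91 = 488 analysed, and 1 − 488/600 = 19% loss.
- To have 50%: effect/SE must equal 2.394, so N = 91 × 2.394² = 522, and 1 − 522/600 = 13% loss.

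**The case against.** The strongest reply is that the section is consistent if read literally. It uses the original sample size as the base both for the doubling and for the 30%. Adding the percentages of 268 gives 590, close enough to an approximate 600, and losing 80 people from 600 leaves 520 with 49.8% power. This stands as far as the total goes: a reader might infer that the stated steps cannot lead to 600, and that is not so. It does not rescue the allowance. On this reading the plan provides for about 13% loss, while a reader will take 30% to be the expected loss in the trial.

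Second, the approximately 50% is attached to the doubling step, before drop-out and baseline adjustment, and the 80% to 268. Correct: neither is presented as the power of 600, and it would be wrong to say the plan claims them for it. The point is only that no interaction power is given for the size actually chosen, and that the figure given is not kept at a 30% loss.

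Third, 420 is a complete-case count. The main analysis imputes, and Fig. 2 includes an assessment at 3 months, so participants with partial data can contribute. This also stands. It makes 40% a conservative figure. How much is recovered cannot be computed from the document.

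Fourth, the plan openly accepts interaction power below 80%, and the main effects are safe. Both are true and they limit the consequence, but they do not correct the number.

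**Conclusion.** The point holds for the interaction only. The 30% allowance either refers to 268, and then covers roughly 13% of the trial, or refers to the doubled sample, and then leads to 627 or to about 690–697 rather than 600. None of the readings worked through above gives both about 600 and a doubled sample protected against 30% loss. At 600, power for an interaction of 1 is about 44% (462 analysed) or about 40% (420 analysed), against 47% computed for the doubled sample and the approximately 50% quoted for it.

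This rests on SD 5, correlation 0.3, two-sided alpha of 0.05/3, and the contrast scale confirmed by reproducing the 22%. The 40% also assumes that those lost contribute nothing.

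A reader might go further and infer that the trial is too small for its main purpose. The document does not support that: the sample size was built on the main effects, which keep 97–98% power for an effect of 2. Nothing here calls for a larger trial. It is a correction worth making to a design figure for one of the three primary parameters.

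**What to change.** Keep 600 and rewrite the end of the Sample size section as one chain that can be reproduced:

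- State which number the 30% is applied to, and whether it means multiplying by 1.3 or dividing by 0.70.
- Replace the approximately 50% with the interaction power expected at 600 after the assumed loss. With correlation 0.3 this is about 44% if 462 are analysed and about 40% if 420 are. Note that 40% is conservative because the main analysis uses multiple imputation.
- Give about 97% power for a main effect of 2 beside it, with 420 analysed.
- If the sponsor in fact expects to lose only about 80 people, say that this is 13% of 600. About 50% can then stand, with baseline adjustment included.

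The cost is a few sentences. Enrolment, design and analysis do not change; one stated power becomes less favourable.

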### Description of interventions

All participants are offered guided exercise for 6 months. This is equal to the most extensive adjuvant treatment period with the exception for endocrine therapy which may continue up to 10 years (for persons with breast cancer). It is also an appropriate period of time to achieve physical exercise effects and to establish a physically active lifestyle [22, 38]. Trained coaches will guide both resistance and endurance exercise.

### Resistance training

The resistance training will be performed at public gyms during two supervised sessions per week. During the first six weeks after inclusion the participants become familiar with the exercises and tests as well as how to use the Omni-scale for self-reported perceived exertion [39] included in the resistance program. During these six weeks, there will be a progression in sets and power output as well as a reduction in the number of repetitions, resulting in each participant having an individualized program. The following exercises are included in the program and performed on machines; seated leg press, chest press, leg extension, seated row, seated leg curl, and seated overhead press using dumbbells. In addition, participants are instructed to do the following core exercises on a regular basis: sit-ups, the plank, bird-dog and pelvic floor exercises.

The low-to-moderate intensity group exercises at 50% of six- (the first weekly session) and ten repetitions maximum (the second weekly session) corresponding to 12 and 20 repetitions in three sets (reporting 5–7 on the Omni-scale for perceived exertion (39)). Rest periods between sets are two and one minute for the two sessions, respectively. The high intensity group exercises at six- (the first weekly session) and ten repetitions maximum (the second weekly session) corresponding to six and 10 repetitions in three sets (reporting 9–10 on the Omni-scale for perceived exertion (39), with the last set continuing to failure. Rest periods between sets are two and one minute for the two sessions, respectively. Relative exercise intensity is adjusted over the remaining intervention period according to repeated measures of six- and ten repetitions maximum.

### Endurance exercise

The first six weeks after inclusion the participants familiarize themselves with the use of the heart rate monitor and perceived exertion using the Borg-scale [40] for monitoring of exercise intensity and perceived exertion. Four endurance sessions are conducted at the gym and supervised by a coach. Thereafter, the endurance exercise is home-based and followed up by a coach. All participants are instructed to warm-up for approximately 10 min at moderate intensity before each endurance session. The participants are instructed to wear the heart rate monitor during every session and report perceived exertion in a diary. Exercise frequency is recommended to be 2–4 times a week. The low-to-moderate intensity group do continuous-based exercise (running, cycling, walking uphill or any other endurance-based activity) in bouts of at least 10 min at an exercise intensity of 40–50% of the heart rate reserve. The main aim is to reach 150 min of moderate intensity per week. The high intensity group conduct high-intensity interval exercise at an exercise intensity of 80–90% of the heart rate reserve (at the end of the 3rd session) with two minutes exercise (running, cycling, walking uphill or any other endurance-based activity) and two minutes rest between sessions. The participants start with five sessions, increasing to six after the six weeks familiarization period, thereafter adding one session every fourth week until 10 sessions are reached as the maximum, corresponding to 75 min of vigorous intensity per week.

